## Abstract

**Background:** Age-related problems such as chronic diseases, functional limitation and dependence, reduce the quality of life in the elderly, and increase public spending in health. It has been established that physical activity plays a fundamental role in the health of the elderly. The whole body electromyostimulation (WB-EMS) could be a successful methodology as high-intensity training to improve the physical fitness of older people.

**Methods:** A minimum of 13 women between 55 and 70 years old will be randomized in two groups. The exercise with WB-EMS group (EX + WB-EMS) will conduct a resistance strength training program with superimposed WB-EMS while the exercise group (EX) will perform only resistance strength and aerobic training. Balance, strength, flexibility, agility, speed, and aerobic performance (EXERNET battery and progressive resistance test), as well as body composition, blood parameters and physical activity reporting (IPAQ-E) will be assessed to analyze the effects of whole body electromyostimulation in the physical fitness and the health in postmenopausal women.

**Discussion:** Innovative and scientifically well-designed protocols are needed to enhance the knowledge of the body's responses within this training methodology which is being used by a big quantity of population. This trial will provide evidence on the effectiveness of whole-body electromyostimulation in physical fitness and health in elderly women.

**Trial Registration:** ISRCTN15558857 registration data: 27/11/2019 (retrospectively registered).

## Background

In recent years, the aging of the world population is increasing at an accelerated rate. In 2017, world population over 60 years old was of 962 million people, which doubled the 1980 figures when there were 382 million. In 2050 the number of elderly people is expected to reach 2.1 billion (1). Two key factors influence the aging of the population. The first one is the increase of life expectancy: on average, people around the world are now living longer. The second one is the decrease of fertility rates (2). Aging is associated with a decline of physical fitness, which has a negative impact on their quality of life and increases their level of dependence (3). As a result, global concern is being generated, both for what aging means for the health of the elderly, and the increase in public spending associated with it (4).

Faced with this situation, many governments are beginning to adopt policies for the prevention, reduction and treatment of diseases derived from advanced age to promote healthy aging (5). It has been established that physical activity plays a fundamental role in the prevention and treatment of age-related problems such as chronic diseases, functional limitation and dependence, which also makes it a facilitating element of a good quality of life (6, 7). In fact, physical activity has been presented as an excellent medicine to prevent and treat various chronic diseases derived from aging (8).

Succinctly, there are several aspects related to physical fitness affected by aging whose impact can be reduced with adherence to physical activity programs. These benefits have been observed particularly in the postmenopausal woman (9), whose hormonal status enhances the risk of diverse health diseases (10). One of the most widespread consequences is sarcopenia. Sarcopenia is the major cause of falls and inability to perform typical daily life activities. It increases dependence, morbidity and death probabilities (11, 12). The decrease in strength, coupled with the balance deficit and instability in gait are the greatest risk factors for falls in older people (13). Sarcopenia has a high prevalence in postmenopausal women, leading to mobility restriction, functional impairment, physical disability and fractures (14). As a solution to this physical decline, it has been established that there is clear evidence of exercise's effectiveness as prevention and remedy against physical frailty, sarcopenia (15, 16), loss of balance and gait difficulties (17, 18). For this reason, the key components of preventing falls training include muscular strength, in addition to balance, walking displacement skills and flexibility (19).

Aging is also the biggest risk factor associated with cardiovascular diseases (20) and due to this, it has been established that age is a facilitating element of metabolic syndrome. As a result of the aging population, cardiovascular problems generate more deaths in Europe than any other cause. In many countries, it even doubles the number of deaths caused by cancer (21). The evaluation of aerobic performance can predict cardiovascular problems (22, 23). Hence, reliable and quality of evidence has established the benefit of cardiorespiratory exercise as a prevention and treatment of cardiovascular diseases (24, 25), contributing decisively to healthy aging (26). In fact, metabolic syndrome is described as an association of cardiovascular risk factors and high levels of HDL cholesterol and triglycerides (27). Exercise as an intervention for patients with metabolic syndrome leads to improved coronary artery disease risk factors, including atherogenic dyslipidemia, blood pressure, and fat metabolism (28).

Parallel to these decreases in strength and cardiorespiratory capacity, older people also experience decreasing body composition and agility with advancing age, which significantly limits their ability to perform daily activities (29). This is where exercise can play a role of great social relevance, since adherence to physical activity programs has been associated with improvements in body composition (30–32), agility (33, 34) and functional capacity (35–37).

Apart from the previously commented diseases, blood tests allow the detection of some other ones which increase with age. On one hand, aging is a risk factor for increased insulin resistance, which makes the glucose levels appear high. This plays an important role in the development of type 2 diabetes (38–40). Physical activity has shown great effectiveness in the prevention and treatment of this disease through programs aimed at the development of strength (41) and aerobic resistance (42, 43). On another hand, the prevalence of thyroid disorders increases with age and the most common thyroid disease in older individuals is hypothyroidism what can be observed in high levels of thyroid-stimulating hormone (TSH) (44). Concretely in women, it has been demonstrated that hypothyroidism is related to low physical activity levels (45).

Despite all the benefits it offers as compensation for the deterioration of physical fitness and health, physical activity has been a resource in critical disuse as a preventive and efective strategy for healthy aging (46). Mainly, sedentary behavior is primarily observed in older people. In fact, they spend 65–80% of their waking time in a sitting position (47). Therefore, to overcome sedentary lifestyles and promote adherence to physical exercise in the elderly, it will be necessary for health authorities to generate physical activity programs with an attractive profile. This programs should provide easily perceived benefits and should enjoy good social support (48).

In recent years, high-intensity training programs have been developed with older people, successfully developing increments in strength (49–53) and resistance (54, 55). Thus, it is possible that whole-body electromyostimulaiton (WB-EMS), as a training method that facilitates a high intensity of charges, could be an appropriate methodology for the exercise of this population group. Traditional local EMS is based in the application of a rectangular, biphasic and symmetrical electrical current to defined muscles by placing on them single surface electrodes. The direct electrical impulse produces muscle contraction by transcutaneous peripheral nerve stimulation (56). Recently, through some technical developments, EMS progressed to WB-EMS by using a suit in which electrodes are strategically placed on the targeted muscles. The WB-EMS devices generally allow the simultaneous activation of the muscles in thighs, arms, buttocks, abdomen, chest, lower back, upper back, wide dorsal, and two auxiliary channels of free choice. The total electrode area is 2,800 cm^2^ (57). Kemmler et al. (58) compared the effects of a WB-EMS training with those of a traditional high-intensity interval training, concluding that both programs showed the same effectiveness in improving the physical condition of sedentary men with cardio-metabolic risk. Following this line of research, the present study has raised the possibility of using this methodology as high-intensity training to improve the physical condition of older women. Our study will take into account that the WB-EMS guarantees sufficient effort in those unable or reluctant to do it on their own initiative (59).

Previous studies have analyzed the effects of WB-EMS on the health of older people, finding improvements in cardio-metabolic risk and sarcopenia (59–65). In addition, the WB-EMS has established itself as an effective method of physical conditioning, achieving improvements in VO_2_max, Aerobic Threshold, Anaerobic Threshold and Economy in the race (66), maximum isometric strength of the leg extenders, vertical jump, and handgrip strength (58, 59, 65–67).

Unfortunately, the high risk of bias of some of the previous studies leads to little evidence regarding the effectiveness of training with WB-EMS (68). So, there is a need for new studies which ensure the use of protocols compatible with a rigorous scientific methodology. The objective of this study is to analyze, from a broad and multivariable perspective, the influence of a 10-weeks WB-EMS training program on the physical condition and health of postmenopausal women using a 2-arm parallel group design with follow-up.

## Methods/Design

### Experimental Approach

The study is designed as a blinded two-arm randomized trial with parallel-groups and a follow-up. This study protocol is reported following the SPIRIT guideline for standard protocol items in interventional trials (69). The study protocol is registered in the ISRCTN registry (trial-ID: ISRCTN15558857 (70) where all the important modifications will be recorded.

Participants will be blinded and distributed into two groups by a computer random number generator (71), the voluntary exercise with WB-EMS group (EX + WB-EMS) or the voluntary exercise group (EX). The EX + WB-EMS group will conduct a resistance strength training program with superimposed WB-EMS while the EX group will perform only resistance strength training. Participants will be evaluated at the beginning (baseline), at the end of the 10 weeks of intervention (post-test) and 6 months after the end of the intervention (follow-up) (see Figure 1).

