### Participants

The target of this recruitment is post-menopausal women between 55 and 70 years old (400 subjects) with a sedentary lifestyle at least 4 months prior to the study. They will be enrolled in the Ekke sports center in Lleida (Spain). They will be contacted by phone call to be informed about the nature of this study. All of them will be invited to attend an informational meeting where more details will be given on the benefits and possible risks that their participation in the project might entail. The subjects who show interest in their participation will be recruited, according to the exclusion criteria. They will be allocated and informed about their assigned arm by phone call by an external collaborator.

According to the shelf reporting in the IPAQ questionnaire of weekly physical activity, participants should be in a sedentary situation according to the scales provided by the Eurobarometer (74). Those who suffer from heart disease, metabolic disorders, tumor processes, or neurological disturbances will be excluded from this study. All participants will be informed of the details of the study and will sign an informed consent form before starting the investigation. The protocol of this study has been approved by the ethical committee of the Arnau of Vilanova's University Hospital, Lérida, (Spain). Participants will be informed of their voluntary participation. Taking into account the possible discomfort which WB-EMS could generate in the participants, they will be informed of their right to withdraw from the study without any prejudice or harm. The deterioration of the participant's health or any accident that could influence the correct development of the treatment will be reasons that will lead to their exclusion at any stage of the intervention. They will be also assured of their anonymity and the reporting of their views in aggregate form to protect their identities.

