### Interventions

Both groups will train with a frequency of 2 weekly sessions. They will have 48 h of rest between sessions. To ensure the blinding of participants, the EX + WB-EMS group will train on Mondays and Thursdays while the EX group will train on Tuesdays and Fridays. Both groups will perform the same program consisting of endurance tasks and resistance strength exercises, but the EX + WB-EMS group will also implement a superimposed WB-EMS during the training. The training protocols will be supervised by two instructors graduated in Physical Activity And Sports Sciences with wide experience in WB-EMS training. Participants were asked not to make physical efforts outside the training program.

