**Figure 2 F2:**
[figure not shown]
Wiemspro suit and device details.

Since there is evidence that a minimum current frequency of 50 Hz is necessary to cause adaptations in strength training (83, 84), a frequency of 55 Hz will be applied during the strength exercises, with a 60% duty cycle (pulse width: leg, glute 350 μs, lumbar, abdominal, dorsal 300 μs, Trapeze 250 μs, chest 200 μs, arm 150 μs), 800 ms of ascent ramp, and descent ramp of 500 ms. During cardiovascular training on the treadmill, the frequency will be 7 Hz with a duty cycle of 100%.

During the WB-EMS sessions, following a similar procedure used by (60), four levels will be established on a scale from 1 to 10 to control the intensity perception of the electrical current (IPC) in the participants. The levels are from 1 to 4 (mild), from 4 to 6 (moderate), from 6 to 8 (intense), and from 8 to 10 (pain). Participants will give constant information on the IPC during the session. The first 2 weeks, training will be conducted at “moderate” IPC level to promote familiarization and adaptation to the WB-EMS. The remaining 8 weeks of the intervention, the intensity will increase to an “intense” PIC level.

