To verify the effectiveness of WB-EMS, it is essential the isolation of its effects from the ones produced by voluntary contraction. In some of the previous studies, the control group received an intervention that was not equivalent to the one applied in the experimental group (58, 109–112). This procedure prevents the analysis of the WB-EMS's effect by itself. In other studies, the control group did not receive any type of intervention (64, 113), which prevents comparability between treatments. Another study compared two different types of training with WB-EMS, which only allowed the comparison of one treatment with another but prevents the analysis of the effect of the WB-EMS by itself (66). Other studies designed interventions whose control group carried out exercises of the same nature as the experimental group, but their training did not match the volume and frequency of training loads (58, 60, 114, 115). The protocol of the present study intends to carry out an experimental phase in which the interventions of both groups are completely comparable in terms of type of movements and training volume (116–118). It will allow identifying precisely the isolated effect of the WB-EMS.

The expected effects of our WB-EMS application protocol related to the development of physical fitness are based on those found by (112) when carrying out a 12-weeks training program with sedentary men. The authors observed that, except for slight improvements in some physical variables, the changes caused by the WB-EMS training were not superior to those of other exercise programs. Similar results were found by (116) in physically active women. The authors concluded that after 4 weeks of intervention, the WB-EMS training could serve as a reasonable but not superior alternative to classic training regimes. On the basis of this finding, it could be considered that the WB-EMS could be an adequate methodology to guarantee the training intensity necessary to cause positive adaptations in the organism. While it does appear to be as effective as other methodologies such as high-intensity interval training (HIIT), WB-EMS could be a good tool in order to reach the intended training intensity with the absence of abrupt movements and high resistance loads. Thus, it would be an adequate approach to postmenopausal women's physical training.

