In Filipovic et al. (119), Kemmler et al. (58), and Wirtz et al. (118) the effects of WB-EMS on anthropometric parameters were analyzed without finding significant differences between the experimental group and the control group. Regarding the analysis of blood parameters, it could appear that there was some kind of significant improvement in cholesterol levels, as it happens in (109). Due to this, given the results obtained to date, the fact of finding significant changes in the blood parameters of the present study would be possible. In Kemmler et al. (113) no changes in triglycerides, glucose and cholesterol were observed after 26 weeks of training with WB-EMS. Similar results were noted in (80) given that no differences were noted in the analysis of the evolution of testosterone, cortisol, and growth hormone.

The way in which the health professional approaches the proposal of the physical activity program to which the patient is intended to adhere seems to be of great importance. It is necessary to assess correctly the needs of the person to propose appropriate exercise to their characteristics. It will also be crucial for the health professional to know how to clearly convey the need to adopt a healthy lifestyle and plan a good methodology and guidelines that will have to be followed to achieve it (120). To comply with this methodology, this study will hold theoretical lectures in which participants will be informed about the type of physical exercise they will perform during the study. They will be explained in detail the training program that we will carry out with them as well as the benefits it will entail for their health and their quality of life. It has been established that technology-based exercise programs have good adherence and may provide a sustainable means of promoting physical activity and preventing falls in older people (121). Taking these results into account, we hope to obtain satisfactory adherence to physical activity with the sample of this study.

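### The trial is called participant-blinded, yet women are told their arm and only one arm feels and rates a current; the label is wrong and the isolated-effect claim needs limiting.

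*Protocol article*

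**What the plan says.** The Experimental Approach section describes the design in these terms: "The study is designed as a blinded two-arm randomized trial with parallel-groups and a follow-up". It then applies the blinding to the women themselves: "Participants will be blinded and distributed into two groups by a computer random number generator".

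The Interventions section supplies the one mechanism: "To ensure the blinding of participants, the EX + WB-EMS group will train on Mondays and Thursdays". The EX arm trains on Tuesdays and Fridays.

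Other sections describe what the women will know and experience:

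- Participants, on allocation: "They will be allocated and informed about their assigned arm by phone call by an external collaborator".
- Participants, on withdrawal: "Taking into account the possible discomfort which WB-EMS could generate in the participants, they will be informed of their right to withdraw".
- WB-EMS Group Intervention, on the perceived intensity of the current: "Participants will give constant information on the IPC during the session". The target is a moderate level for 2 weeks and an intense level for the remaining 8. The EX arm has the same training without current, and no sham suit or sham current is described.
- Discussion, on the lectures given to participants: "They will be explained in detail the training program that we will carry out with them".

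On what the trial will show, the Discussion says of the matched arms: "It will allow identifying precisely the isolated effect of the WB-EMS". Its closing paragraphs name the isolation of WB-EMS effects as the main advantage of the protocol. The limitations given there concern recruitment of volunteers from one sports center and how far the results generalise.

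**The concern.** A participant is blinded if she does not know which treatment she receives. Training on a different day from the other group does not hide a woman's own treatment from her. A phone call naming her arm discloses it directly, and a suit delivering current that she must rate discloses it again at every session.

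This matters because several outcomes depend on how hard a woman tries or on what she reports. The EXERNET tests and the progressive resistance test need voluntary effort; the latter asks for maximal acceleration. IPAQ-E is self-reported. If women who know they have the added technology try harder or report differently, an arm difference can appear that is not due to the current. Readers who take the blinded label at face value would discount that explanation and rate the risk of bias too low. The Background justifies the trial by the high risk of bias in some earlier WB-EMS studies, so the label carries weight.

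**Working it through.** The documents give no figure to reproduce here. The check compares the statements with one another, and a short illustration of scale follows.

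**1. Claim against mechanism.** Participant blinding is claimed under Experimental Approach. The mechanism under Interventions is separate weekdays. This can keep women in one arm from meeting women in the other; it does not conceal any woman's own allocation.

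**2. Claim against disclosure.** The Participants section has the assigned arm communicated by phone. This alone contradicts the claim, for both arms.

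**3. Claim against experience.** Women in EX + WB-EMS wear the suit, feel the current at a moderate then intense level, and report on it throughout. Women in EX do none of this, and no sham replaces it. So even without the phone call, the WB-EMS arm could not be unaware of receiving current.

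**4. What the comparison isolates.** Both arms do the same exercise, so the arm difference excludes the effect of voluntary training. It still contains the effect of the current together with any effect of knowing that one receives it.

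**5. Which outcomes are exposed.** A count from the Outcomes sections:

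- Effort-dependent or self-reported: 8 EXERNET tests + 4 resistance-test measures (velocity and power, squat and bench press) + 4 IPAQ-E scores (vigorous, moderate, slight, total) = 16.
- Less exposed: 11 body-composition measures (the 12 listed, without height) + 9 blood measures = 20.
- Total 16 + 20 = 36, and 16/36 = 44%. Counting height and estimated muscle mass as well gives 38, and 16/38 = 42%.

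**6. Illustration of scale, under an assumption.** Suppose the current has no effect, but knowing the arm shifts an outcome by b standard deviations. For a two-sided 5% two-group t-test with n per arm, the degrees of freedom are 2n − 2 and the noncentrality is b × √(n/2). For n = 14 and b = 0.3 this is 0.3 × √7 = 0.79. The protocol article gives 14 per arm with the dropout allowance, and its minimum total of 22 gives 22/2 = 11 per arm.

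| Assumed shift b | Rejection, 14 per arm | Rejection, 11 per arm |
|---|---|---|
| 0 | 0.050 | 0.050 |
| 0.1 | 0.057 | 0.056 |
| 0.2 | 0.080 | 0.073 |
| 0.3 | 0.119 | 0.103 |
| 0.5 | 0.247 | 0.201 |

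The values of b are assumptions. The test is a single comparison between arms, simpler than the planned mixed ANOVA, so the table shows scale only.

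**The case against.** The best defence concerns the isolated-effect claim. The Discussion says what it wants to isolate WB-EMS from: the effect of voluntary contraction. It criticises earlier trials for untreated or unmatched controls and answers with arms matched on movements and volume. In that sense the design does what it says, and a reader who infers that the claim fails altogether goes too far. What remains is that the words for precision and assurance exceed what a comparison without a sham can deliver.

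Other strong readings also fail:

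- A reader might infer that most outcomes are compromised. The count is 16 of about 36, a minority. Blood tests are run by a hospital department, and anthropometry by a certified technician.
- A reader might express an expectation effect as a share of the planned d = 0.70. That d comes from hip circumference, a tape measurement, and is not the planned effect on the effort tests.
- A reader might conclude that the primary outcome should be one that needs little effort. The stated objective includes physical condition, which the fitness tests measure. Correcting a label does not require a different outcome.
- The lectures are not said to reveal allocation, and the text does not spell out what the information meeting says about WB-EMS. The case rests on the phone call and the rated current.
- The article does not claim that instructors are blinded. Its silence on assessor blinding may be a matter of condensation, so neither is counted as an error.

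It could also be said that blinded means unaware of the hypothesis or of the other arm's content. The text does not say so, and being told one's arm sits badly with that reading.

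**Conclusion.** The point holds as a contradiction within the protocol article. The participant blinding claimed under Experimental Approach and Interventions cannot stand beside the disclosure under Participants and the rated current under WB-EMS Group Intervention. That conclusion needs no assumption.

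The consequence is limited. The estimate is the effect of adding WB-EMS to the same exercise, including any effect of expectation or motivation. The Discussion's stronger statements are overstated for the effort-dependent tests and IPAQ-E, and less so for blood and body-composition measures. How large the bias might be is unknown; the rejection rates tabulated above rest wholly on assumed shifts. The statistician's blinding, stated under Outcomes and Statistical Procedures, is workable and unaffected, but it does not protect against participants' expectations. The wording must be corrected because readers will judge risk of bias on it.

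**What to change.** 1. Under Experimental Approach and Interventions, describe the trial as open-label for participants with a blinded statistician. Present the different training days as a measure against contact between arms.
2. The Harms section already distinguishes assessment staff from the session instructors. Have those assessment staff run the post-test and follow-up without access to the allocation list, and ask women not to disclose their arm to them.
3. In the Discussion, in both places where isolation is claimed, restate the conclusion as the effect of adding WB-EMS to the same exercise without a sham control, including any expectation effect.
4. Add the lack of participant blinding to the limitations.

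The cost is wording plus a staffing rule for people already in the plan. The trial loses the label of a blinded trial. Interventions, outcomes, sample size and analysis do not change.
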